## Abstract

**Background:**

Diabetes inpatient specialist services vary across the country, with limited evidence to guide service delivery. Currently, referrals to diabetes inpatient specialists are usually ‘reactive’ after diabetes-related events have taken place, which are associated with an increased risk of morbidity/mortality and increased length of hospital stay. We propose that a proactive diabetes review model of care, delivered by diabetes inpatient specialist nurses, may contribute to the prevention of such diabetes-related events and result in a reduction in the risk of harm.

**Method:**

We will conduct a cluster randomised feasibility study with process evaluation. The proactive diabetes review model (PDRM) is a complex intervention that focuses on the prevention of potentially modifiable diabetes-related harms. All eligible patients will receive a comprehensive, structured diabetes review that aims to identify and prevent potentially modifiable diabetes-related harms through utilising a standardised review structure. Reviews are undertaken by a diabetes inpatient specialist nurse within one working day of admission. This differs from usual care where patients are often only seen after diabetes-related harms have taken place. The trial duration will be approximately 32 weeks, with intervention delivery throughout. There will be an initial 8-week run-in phase, followed by a 24-week data collection phase. Eight wards will be equally randomised to either PDRM or usual care. Adult patients with a known diagnosis of diabetes admitted to an included ward will be eligible. Data collection will be limited to that typically collected as part of usual care. Data collected will include descriptive data at both the ward and patient level and glucose measures, such as frequency and results of capillary glucose testing, ketonaemia and hypoglycaemic events. The analysis aims to determine the fidelity and acceptability of the intervention and the feasibility of a future definitive trial. Whilst this study is primarily about trial feasibility, the findings of the process evaluation may lead to changes to both trial processes and modifications to the intervention. A qualitative process evaluation will be conducted in parallel to the trial. A minimum of 22 patients, nurses, doctors, and managers will be recruited with methods including direct non-participant observation and semi-structured interviews. The feasibility of a future definitive trial will be assessed by evaluating recruitment and randomisation processes, staffing resources and quality of available data.

**Discussion:**

The aim of this cluster randomised feasibility trial with a process evaluation is to explore the feasibility of a definitive trial and identify appropriate outcome measures. If a trial is feasible and the effectiveness of PDRM can be evaluated, this could inform the future development of inpatient diabetes services nationally.

**Trial registration:**

UK Clinical Research Network, 51,167. ISRCTN, ISRCTN70402110. Registered on 21 February 2022.

**Supplementary Information:**

The online version contains supplementary material available at 10.1186/s40814-024-01507-2.

## Background

In the UK, it is estimated that 1 in 15 people currently have diabetes, and 1 in 6 hospital beds is occupied by someone with diabetes [9]. Hypoglycaemia (blood glucose < 4.0 mmol/L) and hyperglycaemia (blood glucose > 11 mmol/L) among hospitalised patients with diabetes increase the risk of adverse health-related outcomes such as hospital-acquired infections, increased length of stay and increased in-hospital mortality [17]. The National Diabetes Inpatient Audit Group (NaDIA) reported that in England, target glycaemic control was achieved in less than half of all hospital inpatient days. ‘Good’ glycaemic control has been defined by NaDIA as no episodes of hypoglycaemia < 4.0 mmol/L and no more than 2 episodes of hyperglycaemia > 11.0 mmol/L. Additionally, 20% of people with diabetes in the hospital experience hypoglycaemia, with 8% of these classed as severe [20]. Inpatient hypoglycaemia is associated with a 3-day increased length of hospital stay and increased risk of in-hospital mortality [13].

The National Quality Board [21] highlighted the importance of ‘getting the right professional, with the right skills, to review the right patient, at the right time and in the right place’. However, little is known about what interventions are likely to be effective in achieving this. Of the service developments or service evaluations reported, most are complex interventions of which few have undergone methodologically rigorous evaluation [22] and [14]) many involved additional staff resources [23] and [16]), which might explain the improvement in outcomes reported. None have undertaken a process evaluation or provided an assessment of which of the multiple components of the intervention were likely to be the most effective [12]. Improvements in outcomes reported include a reduction in mild and severe hypoglycaemia and medication errors, increased staff knowledge, confidence and satisfaction; reduced length of stay [23] and [14]), a reduction in delayed discharges; avoidable admissions and inappropriate discharge plans [16], and a reduction in hyperglycaemia and hospital-acquired infections [12].

We propose that a proactive model of care by the diabetes inpatient specialist nurses (DISNs) within one working day of admission has the potential to improve inpatient diabetes management by:Reducing preventable diabetes-related adverse eventsImproving levels of support offered to non-diabetes specialist colleagues (doctors/nurses/AHPs)Working with patients to create their inpatient diabetes management planIncreasing awareness of diabetes management in hospitals through increased visibility of the diabetes team in the wardsSupporting primary teams to be more knowledgeable and effective in managing diabetes

## The intervention—proactive diabetes review model (PDRM)

The proactive diabetes review model (PDRM) is a complex intervention that combines all the components of the usual care provided by a DISN at the first review, and applies the principles recommended by the national quality board by making changes to the timing, focus and ambition of the review. PDRM will be delivered by DISNs for patients with diabetes admitted to the hospital. The PDRM consists of a patient-centred diabetes assessment undertaken within one working day of admission to an included intervention ward and aims to identify modifiable risks and prevent diabetes-related harm (see Table 1). The intervention will consist of a single visit for individual patients; all care after this will fall in line with usual care. Recommendations will be based on best clinical practice, at the discretion of the professional undertaking the review.

**Table 1 Tab1:** PDRM intervention components

Category	Detail	Outcome data source
An initial bedside assessment of the patient	Current and historical medications Feet and injection sites as appropriate Usual diabetes care provider Diabetes education history Patient-reported history of home glucose level	Reviewing the medical notes and trial paper case report forms
A review of routinely collected investigations	Glucose monitoring Ketone monitoring where applicable HbA1c Annual review processes, TSH, urea, creatinine, ACR	Reviewing the medical notes and electronic data exports
Recommendations resulting from the shared decision-making process	Links to relevant policies and guidance where appropriate Documented in the patients’ medical records	Reviewing the medical notes and trial paper case report forms
Provision of any appropriate patient information	Leaflets App recommendations Other patient literature Signposting to any relevant patient-specific resources	Reviewing the medical notes and trial paper case report forms
Handover of recommendations to the patient and patient’s primary team	Admitting speciality doctor Ward nurses	Reviewing the medical notes and trial paper case report forms
Triage	No further follow-up Further follow-up by the diabetes specialist team—ongoing reviews will be managed in line with usual care	Reviewing the medical notes and trial paper case report forms

The overall responsibility for the patient will remain with the primary ward team (patients admitting specialty doctors and ward nurses, as is currently the case). Therefore, as part of this process, support for the patient’s primary team will be provided through expert recommendations, ‘on the spot’ education as needed, and an increased visibility of the diabetes inpatient specialist nurses on the wards. After the first review, the patient will then be triaged into one of two groups: no further review required (re-refer as needed) or ongoing review. PDRM differs from usual care by proactively reviewing all patients with diabetes, not just those who have been referred. Other differences include the structure, timing and aims of the review itself.

It is anticipated that reviews will take between 15 and 45 min depending on complexity. An example of a non-complex review could be an inpatient with diet-controlled diabetes and no expected glycaemic disruption. A complex review for example would include inpatients treated with agents known to cause hypoglycaemia and/or admitted with complex health needs leading to treatment, such as corticosteroids, known to interfere with glucose levels. Diabetes treatment alone will not be used to indicate individual risk.

## Service evaluation of the model

In 2018, we undertook a service evaluation of PDRM at the Cambridge University Hospitals NHS Foundation Trust (CUHFT). The service evaluation aimed to refine the model and investigate the potential impact on both the service and patients. All patients with diabetes in eight wards received a proactive review by a DISN within one working day of admission. No adjustments to the model were made. The outcome data that was collected from the intervention wards were compared to the same eight wards, for the same 4 months (November to February) during the previous year using routinely available retrospective data. The results showed a 30% increase in the number of first reviews being undertaken, with a decrease in hypoglycaemia episodes, shorter length of hospital stay and improved staff satisfaction [14]. Kyi et al. [12] also report the potential for improved outcomes utilising a proactive approach, but in both cases, there is no information regarding implementation, contamination or intervention acceptability, which is why further process evaluation is warranted. The definition of acceptability in this trial includes how acceptable the intervention (the timing and content of the diabetes review and form of delivery) and trial methods (processes of recruitment and data collection) are for people with diabetes in the hospital, the ward-based staff caring from them and the diabetes inpatient teams delivering the diabetes-related care.

Following the MRC framework for developing and evaluating complex interventions, we are now undertaking feasibility testing. The definition of feasibility testing in this trial is to explore the proposed trial design, methods and analysis prior to a definitive trial. Feasibility testing is essential because of what remains unknown [7].

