#### Trial outcomes

The following are the trial outcomes:Number of days, per patient admission, where glucose testing completedIncidence of hypoglycaemia (rate of biochemical hypoglycaemic episodes defined as blood glucose < 4.0 mmol/L during hospital stay)Incidence of hyperglycaemia > 15.0 mmol/LIncidence of positive ketones (blood ketone ≥ 1.5 mmol/L)Incidence of hospital-acquired foot ulcerationLength of hospital stay (total number of inpatient days)

The feasibility of a future definitive trial will be determined by the following:Evidence that recruitment at both the cluster and individual levels can be achievedEvidence that the intervention can be delivered. The proportion of patients who received the proactive reviewEvidence of availability of trial outcome data

We will analyse our feasibility data for recruitment and intervention delivery against the progression criteria as set out in Table 2. Where the criteria set out in the green column are met, the study will be considered feasible. If only the criterion in the amber column is met, feasibility will be dependent on whether a definitive trial could address this methodologically, drawing on the process evaluation data. If the amber criteria are not met, the study will not be considered feasible. For progression to a definitive trial, the findings must demonstrate that all five green or amber criteria have been met, with strategies to address where we have not met green criteria.

**Table 2 Tab2:** Progression criteria

	Green	Amber	Red
Cluster recruitment to target (8 wards)	90–100%	70–89%	< 70%
Participant recruitment: proportion of approached and eligible patients consenting to participate	90–100%	70–89%	< 70%
Intervention delivery: proportion of patients that received the intervention (intervention arm participants only)	90–100%	70–89%	< 70%
Median time from identification to receiving a review by a diabetes specialist (intervention arm participants only)	Within one working day	One to three working days	Four or more working days
Trial outcome data available	90–100%	70–89%	< 70%

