#### Data collection

Descriptive and outcome data will be collected throughout the 8-week run-in period and 24-week intervention and follow-up period. To reduce patient burden, a pragmatic approach to data collection will be adopted by restricting all quantitative data to information routinely collected as part of clinical care. Data will be extracted after the participant has consented and the episode of care completed (i.e. after hospital discharge). Data extraction will include a mix of reviewing the medical notes, electronic exports and trial paper case report forms. Ward-level data will be provided by the ward managers through a spreadsheet requested monthly.

Descriptive statistics and outcome measures will be described at baseline (run-in phase) and trial end. Data will be collected for the duration of a participant’s hospital stay. Their inclusion in either the baseline or trial end analysis will depend on the time point of their admission during the trial. Baseline analysis will use the data of participants admitted during the run-in phase (weeks 0–8) and outcome analysis of the data of those participants admitted during weeks 9 to 36.

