#### Statistical analysis

Groups at baseline will be described using summary statistics at both ward and patient levels. Changes from baseline will be described within and between the two trial arms from run-in to follow-up periods. The purpose of the analysis is (1) to describe the potential effect via confidence intervals allowing for the clustered design, (2) as a way of trialling an analytic plan for a future definitive trial if the proposed study suggests one is feasible and (3) the extent and distribution of missing data will be reported for consideration as to how to manage this in a definitive trial. Statistical analysis will be completed using the latest version of STATA® with the trial statistician (AC). No interim analysis of trial outcomes between arms is planned.

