#### Sample size

The trial outcome measures are designed to address the research aims and objectives. This exploratory feasibility trial is not statistically powered to detect the superiority of treatment effects. A cluster-level recruitment target of eight randomised wards on a 1:1 basis has been chosen to allow sufficient recruitment and diversity in the population to answer the study questions.

A participant-level recruitment objective has not been set as this is one of the feasibility outcomes. However, based on the service evaluation, we anticipate 500–800 potentially eligible participants to be identified with 250–500 being recruited.

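### The glucose-testing outcome is a raw count of tested days per admission, capped by length of stay, so shorter stays under PDRM would pull it down and could hide or reverse a gain in testing coverage

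*Protocol article*

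**What the plan says.** The abstract of the protocol article says that the data will include "frequency and results of capillary glucose testing". The Trial outcomes section turns this into a count for each admission: the number of days on which glucose testing was done. No denominator is attached. Length of stay, in total inpatient days, appears in the same list as a separate outcome, and the two are not linked.

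The hypoglycaemia outcome in that list is worded differently, as the "rate of biochemical hypoglycaemic episodes defined as blood glucose < 4.0 mmol/L during hospital stay".

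The Data collection section fixes the observation window: "Data will be collected for the duration of a participant’s hospital stay". The Statistical analysis section gives as one purpose "to describe the potential effect via confidence intervals allowing for the clustered design", and as another the rehearsal of an analysis for a definitive trial.

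On the intervention's likely effect on stay, the section on the service evaluation reports a 30% increase in first reviews, "with a decrease in hypoglycaemia episodes, shorter length of hospital stay and improved staff satisfaction". The comparison was with the same eight wards "for the same 4 months (November to February) during the previous year using routinely available retrospective data". No size is given for the reduction in stay.

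**The concern.** Each admission is observed for its whole stay, so the largest possible value of the outcome is the length of that stay. The count combines two quantities: how long the patient stayed, and on what share of those days glucose was tested. Only the second describes how completely glucose was monitored.

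This would matter little if stay were unrelated to the intervention. But the article itself reports shorter stays under PDRM and lists length of stay as a trial outcome. If stay differs between arms, the difference in tested days no longer estimates the difference in testing. A shorter stay counts against the intervention arm even if testing is unchanged or better.

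At stake are the estimate and confidence interval for this outcome, and the judgement of whether the measure suits a definitive trial. Choosing suitable outcome measures is a stated aim of the study.

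**Working it through.** The article states no effect size, mean stay or testing coverage for this outcome, so there is no figure of its own to reproduce. The check is algebra with assumed inputs.

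**Inputs.** L0 and L1 are mean stay in days under usual care and PDRM. p0 and p1 are the shares of inpatient days with a glucose test. All four are assumptions. Coverage is treated as independent of length of stay.

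**Formula.** Expected count C = L × p, so C1/C0 = (L1/L0) × (p1/p0).

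- If L1 < L0, the ratio of counts is always below the ratio of coverages. The outcome is pulled down whatever the size of the cut.
- The sign reverses (p1 > p0 but C1 < C0) only if p1/p0 < L0/L1. Break-even coverage is p1 = p0 × L0/L1.
- Since p1 cannot exceed 1, the count must fall whatever happens to testing if p0 > L1/L0.

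**Examples with L0 = 8 and p0 = 80%, so C0 = 6.4 tested days.**

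- Stay 7 days, coverage unchanged: 7 × 0.80 = 5.6. Testing is the same, but the count falls by 0.8 days.
- Stay 7 days, coverage 90%: 7 × 0.90 = 6.3. Here p1/p0 = 1.125 is below L0/L1 = 8/7 = 1.143, so a 10-point gain appears as a small fall. Break-even is 6.4/7 = 91.4%.
- Stay 7.4 days, coverage 90%: 7.4 × 0.90 = 6.66. Here 1.125 exceeds 8/7.4 = 1.081, so there is no reversal. The gain is muted: coverage rises by 12.5% in relative terms, the count by 6.66/6.4 − 1 = 4.1%. Break-even is 6.4/7.4 = 86.5%.

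**A wider range, with L0 = 10 days and coverage rising from 70% to 80%** (count 7.0 under usual care; relative rise 0.80/0.70 − 1 = 14.3%):

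| Assumed cut in stay | Relative rise in coverage needed to break even | PDRM count | Direction shown |
|---|---|---|---|
| 5% | 5.3% | 9.5 × 0.80 = 7.6 | rise |
| 10% | 11.1% | 9 × 0.80 = 7.2 | rise |
| 20% | 25.0% | 8 × 0.80 = 6.4 | fall |
| 30% | 42.9% | 7 × 0.80 = 5.6 | fall |

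**With a denominator.** Tested days divided by inpatient days gives 70% against 80% in every row, and 80% against 90% in both examples where coverage rises. The result no longer depends on the cut in stay.

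**The case against.** Several objections have force.

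- **Reversal is not established.** A reader might infer that better testing will be recorded as less testing. The documents do not support that. The service evaluation was an uncontrolled before-after comparison that gives no size for the cut in stay, and nothing is said about coverage. Modest cuts leave the sign intact, as shown above.
- **The article cannot supply the missing size.** The Background says "Inpatient hypoglycaemia is associated with a 3-day increased length of hospital stay" and that 20% of inpatients with diabetes have hypoglycaemia. Multiplying these gives 0.20 × 3 = 0.6 days. Reading that as a PDRM effect would require the association to be wholly causal and every such episode to be prevented. If half were prevented, the cut would be 0.3 days and break-even coverage 6.4/7.7 = 83.1%.
- **The count need not be mostly length of stay.** Simulations with a mean stay of 8 days and average coverage of 80% put 81% to 93% of the count's variance down to stay. Those inputs are all assumed, and the figure describes variation between patients, not bias between arms.
- **No direction is stated.** The article does not say that more tested days is better. This weakens talk of a wrong sign, but the count still mixes two quantities.
- **No decision turns on the estimate.** Table 2 judges trial outcomes only by data availability, and the Sample size section says "This exploratory feasibility trial is not statistically powered to detect the superiority of treatment effects". A reader might infer that progression would be distorted; the criteria do not allow that reading.
- **An analysis plan not shown may add an offset.** It may, and the planned comparison with the run-in period would ease stable differences in stay between wards. Neither changes the outcome as defined, and the run-in comparison does not remove a shortening caused by PDRM.

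These points limit the consequence. They leave the definition itself as a count capped by length of stay.

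**Conclusion.** The point holds as a defect in the outcome definition. As worded, the outcome combines testing coverage with length of stay. If PDRM shortens stay, the between-arm difference is biased downward relative to the change in coverage.

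Whether the bias only mutes a gain or reverses it depends on whether L0/L1 exceeds p1/p0. Under the assumed 8-day, 80% baseline and a rise to 90% coverage, a 1-day cut reverses the sign (6.4 to 6.3) and a 0.6-day cut does not (6.4 to 6.66). These figures illustrate the mechanism and do not predict this trial's result. They rest on assumed stays and coverages and on coverage being independent of stay.

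The consequence is limited to the description of this one outcome and its value as a candidate for a definitive trial. It is worth correcting because the study is meant to try out its outcomes and analysis.

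**What to change.** In the Trial outcomes section, replace the count with the proportion of inpatient days on which at least one glucose test was recorded: tested days divided by inpatient days in the same window, with admission and discharge days counted the same way in both. Analyse it as a proportion, or as a count of tested days with inpatient days as an offset, allowing for clustering by ward. Keep the raw count as a descriptive line only.

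The cost is about one sentence in the outcome definition and a matching line in the analysis. Tested days and inpatient days are both already listed as outcomes and taken from routine records, so no new data are needed.
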